### 1.8 Primary outcome measure

The primary outcome was the rate of responders to treatment: a patient will be considered as a responder if he satisfies two conditions: (1) a decrease of at least 30% of the score of abdominal pain (11-point NRS) compared with the score before treatment, and (2) a significant global improvement defined by a score of 4 or 5 on the SGA scale.

### 1.9 Secondary outcome measures

Secondary outcome measures include:

- The quality of life was evaluated by the GQLI and EQ-5D-3L (EuroQol group), which assess the physical and mental health of IBS patient.
- The severity of IBS symptoms was evaluated by IBS-SSS questionnaire and Bristol scale.
- The safety of ethosuximide was evaluated by daily collection of adverse effect by patient.
- Analgesic consumption throughout the study.

## 2. Analysis plan

### 2.1 Generality

All analyses will be performed with the use of Stata software (version 15, StataCorp, College Station, USA) before the breaking of the randomization code, according to International Conference on Harmonization-Good Clinical Practice guidelines.

The primary analysis will be conducted in the intention-to-treat (ITT), modified intention-to-treat (mITT) and per-protocol populations. We will perform a per-protocol analysis on the primary outcome. The criteria for including patients in the modified ITT and in the per-protocol populations, respectively, are provided below.

Baseline variables will be reported as numbers and percentages for categorical variables and medians with interquartile ranges (IQRs) for continuous variables. As according to the CONSORT 2010 statement, group differences in baseline variables will not be compared using significance testing unless specifically requested by peer reviewers.

### 2.2 Study population

Intention-to treat (ITT) population: All randomised patients.

Because the study is a proof of concept, this population will not be analysed in the IBSET study.

Modified intention-to-treat population (mITT): All randomised patients except patients who:

- Patients who withdrawn consent for the use of data
- OR
- Patients who did not have any of the interventions
- OR
- Patients who did not be eligible for randomisation according to inclusion/non-inclusion criteria (screen fail or absence of baseline pain intensity [primary outcome])
- OR
- Patients with major deviation (primary outcome not available, non-compliance)

Per-protocol population: All randomised patients except patients having one or more major protocol violations defined as:

- Patients who accidentally received the wrong treatment
- OR
- Patients who discontinued study treatment
- OR
- Patients who did not have any of the interventions
- OR

- Patients who withdrawn consent for the use of data

OR

- Patients who did not be eligible for randomisation according to inclusion/non-inclusion criteria (screen fail or absence of baseline pain intensity [primary outcomes])

OR

- Patients with major deviation (primary outcome not available, non-compliance)

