#### Genetic analysis of cytochromes P450:

A blood sampling (1 tube of 6 ml) will be performed for the genetic analysis of the genes coding for CYP3A4 and CYP2E1, involved in the metabolism of ethosuximide. This genetic analysis will make it possible to demonstrate the existence (or not) of slow / fast metabolizers in our studied population. The demonstration of slow / rapid metabolizers will enable us to carry out a more precise analysis on the therapeutic efficacy of ethosuximide.

These blood samples will be strictly used in this study and a specific document informing the patient and obtaining his authorization will be provided during the first visit (D0-7).

Analgesic and antispasmodic/regulators transit consumption: Drugs consumption for IBS will be evaluated throughout the study

Safety: Any adverse events were collected daily by the patient and during the planned phone calls by investigators (every 7 days). Adverse events are categorized according to their type, intensity and treatment related by investigators. Due to the long half-life of ethosuximide (60h), a phone call, within 3 weeks after stopping treatment, will be allowed to recover any adverse effects.

Study discontinuation rate will be evaluated and compared in the two treatment arms.

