#### Data collection, management, and analysis:

##### *Data collection methods*

Data entry will be made by the investigators and CRA of each clinical centre, at each planned visits and during the ambulatory period.

Data entry will be centralized in the coordinating centre (CHU Clermont-Ferrand), from an electronic case report form (e-CRF, Ennov Clinical, France) filled-in during site visits.

All patients will be analysed (intent to treat analysis). However, if a major deviation from the protocol (non-respect of co-occurring treatment, inclusion / exclusion criteria and the study design) only safety data will be evaluated.

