##### *Statistical methods*

Statistical analyses will be conducted using Stata software (version 13, StataCorp, College Station, US). A two-sided p-value of less than 0.05 will be considered to indicate statistical significance (except interim analysis).

Intent-to-treat (ITT), mITT, and per-protocol (PP) analyses were performed for the primary endpoint and expressed as relative risks (RR) with 95% confidence intervals (CI). Non-compliant patients were considered non-responders. Responder rates were compared using the chi-squared test and a pre-specified multivariate analysis was performed using a generalized linear mixed model (Poisson regression with a log link and robust variance 26) accounted for fixed covariates (e.g., gender, IBS subtype) and centre-level variability were performed. Primary endpoint components were also analysed with the Hochberg procedure for multiple testing.

Continuous outcomes were assessed with linear mixed models incorporating patient-level random effects (slope and intercept) nested within centre-level random effects. Results were expressed as regression coefficients (standardized mean differences - MD) with 95% CI, based on the interaction between time and randomization group. The normality of residuals from these models was analysed as aforementioned. Safety analysis was conducted with chi-squared or Fisher's exact tests.

Missing data (if any) were imputed using Multiple Imputation by Chained Equations (MICE). Analyses were conducted using Stata 15.0, with a two-sided P value <0.05 considered significant, and the widths of confidence intervals were not adjusted for multiplicity and should not be used as a substitute for hypothesis testing, except for the primary outcome and its composite components. An interim analysis is planned after enrolment of the first 100 patients using the Lan and DeMets rule (East software, Cytel Inc, Cambridge, Massachusetts, US). The type I error is fixed at 0.03 for this interim analysis. In addition, an early intermediate analysis (third of the inclusions) will be also proposed in order to study safety of the initial maximum dose (10 ml/day) and, if necessary, to allow the addition of a therapeutic dose in case of inefficiency.

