Planned subgroup analyses were assess heterogeneity of the effect of ethosuximide on the primary outcome measure in pre-specified subgroups of patients with IBS subgroup and gender. According to usual recommendations, the interactions between group randomization and subgroups was evaluated in regression models (i.e., random-effects models, linear or generalized linear).

A descriptive analysis of stopping and discontinuations in view of dose escalation was considered. A particular focus was done to safety and lose to follow-up. A study of abandonment considered as censored data was proposed using the Kaplan-Meier estimation. The proportional-hazard hypothesis was verified using Schoenfeld's test and plotting residuals.

Finally, a sensitivity analysis was performed and the nature of missing data was studied (missing at random or not). According to this, the most appropriate approach to the imputation of missing data was proposed (MICE, spline interpolation, LOCF, BOCF...).

A two-sided P value of less than 0.05 was considered for statistical significance of all analyzes. The Hochberg procedure was used to adjust for multiple testing of each component of the composite primary outcome ((1) decrease of at least 30% of the intensity of abdominal pain (11-point NRS) compared with the score before treatment and (2) significant global improvement defined by a score of 4 or 5 on the SGA scale). Because of the potential for type 1 error due to multiple comparisons, findings from analyses of secondary endpoints were interpreted as exploratory.

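### No population is named for the safety and discontinuation analyses, and no set that SAP 2.2 leaves open holds every treated patient

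*Combined protocol and SAP*

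**What the plan says.** SAP 2.2 sets out three populations. The first is complete: "Intention-to treat (ITT) population: All randomised patients". The next sentence takes it out of use: "Because the study is a proof of concept, this population will not be analysed in the IBSET study". That sentence carries no limit to efficacy or to any endpoint.

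The other two sets, mITT and PP, both exclude patients who were never treated, who were ineligible or lacked a baseline pain score, who withdrew consent for data use, or who had a major deviation. Major deviation is explained as an unavailable primary outcome or non-compliance. PP alone adds "Patients who discontinued study treatment" and patients given the wrong treatment.

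Other sections differ on ITT. SAP 2.1 states: "The primary analysis will be conducted in the intention-to-treat (ITT), modified intention-to-treat (mITT) and per-protocol populations". The protocol (Statistical methods) states: "Intent-to-treat (ITT), mITT, and per-protocol (PP) analyses were performed for the primary endpoint". The protocol (Data collection methods) says that all patients are analysed by intention to treat, and that after a major deviation "only safety data will be evaluated".

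Safety is a stated objective (SAP 1.2) and a listed secondary outcome (SAP 1.9). On discontinuation, the protocol says, in the safety text under the cytochrome P450 heading: "Study discontinuation rate will be evaluated and compared in the two treatment arms". SAP 2.4 plans a descriptive account of discontinuations and adds: "A study of abandonment considered as censored data was proposed using the Kaplan-Meier estimation". None of these places names a population.

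**The concern.** A programmer working from SAP 2.2 has no usable set that contains every patient who took study drug. A patient who takes ethosuximide, has an adverse event, stops and leaves before week 12 has no week-12 pain or SGA score. Unless that outcome is imputed and counted as available, the patient is in neither mITT nor PP. A patient randomised in error and dosed is in neither set on any reading.

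These are the patients whom safety tables exist to describe. The protocol expects some of them, since its dose-escalation section foresees stopping for intolerance. If the tables were run on the sets left, they would condition on having tolerated the drug or completed follow-up. Adverse events that led to withdrawal would be under-counted, more so in the less well tolerated arm, and the discontinuation analyses would lose their own events.

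**Working it through.** **1. The plan's own figure.** The point disputes no stated number. The arm size used below reproduces: 130 / (1 − 0.10) = 144.4, rounded up to 145 per arm.

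**2. Where a treated patient who stops ends up, by SAP 2.2**

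| Patient | ITT | mITT | PP |
|---|---|---|---|
| Stops, leaves, no week-12 outcome | in, but set not analysed | out | out |
| Stops, has week-12 outcome, not classed non-compliant | in, but set not analysed | in | out |
| Stops, classed non-compliant | in, but set not analysed | out | out |

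PP therefore removes all stoppers, and mITT removes some of them.

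**3. Size if all stoppers are deleted.** The documents give no adverse-event (AE) or stopping rates, so every input here is an assumption: 145 treated per arm, every stopper has an AE, and a proportion b of non-stoppers has an AE in both arms. With s stoppers in an arm, the all-treated AE rate is [s + b(145 − s)] / 145. With stoppers deleted it is b in both arms. The hidden difference is (1 − b)(s_active − s_placebo) / 145.

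| Stoppers, active v placebo | b | AE rate, all treated | Hidden difference |
|---|---|---|---|
| 7 v 7 (5% v 5%) | 0.30 to 0.50 | equal in the two arms | 0 points |
| 14 v 7 (10% v 5%) | 0.50 | 54.8% v 52.4% | 0.50 × 7/145 = 2.4 points |
| 29 v 7 (20% v 5%) | 0.40 | 52.0% v 42.9% | 0.60 × 22/145 = 9.1 points |
| 44 v 14 (30% v 10%) | 0.30 | 51.2% v 36.8% | 0.70 × 30/145 = 14.5 points |

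(Percentages are rounded to whole patients.) In the first row no difference is hidden, but both rates are understated by 2.4 points (52.4% read as 50%) to 3.4 points (33.4% read as 30%).

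**4. Size if half the stoppers stay, one possible mITT.** Take 29 v 7 stoppers and b = 0.40.
- AE, active: (46.4 + 14.5) / 130.5 = 46.7%. AE, placebo: (55.2 + 3.5) / 141.5 = 41.5%. The difference is 5.2 points instead of 9.1.
- Discontinuation: 14.5/130.5 = 11.1% v 3.5/141.5 = 2.5%, instead of 20.0% v 4.8%.

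**5. A true 20-point AE difference with every early leaver deleted.** The observed rate is (AE rate − rate leaving for an AE) / (1 − rate leaving for an AE).
- AE 60% v 40%, leaving 15% v 3%: 0.45/0.85 − 0.37/0.97 = 52.9% − 38.1% = 14.8 points.
- AE 50% v 30%, leaving 20% v 5%: 0.30/0.80 − 0.25/0.95 = 37.5% − 26.3% = 11.2 points.
- AE 60% v 40%, leaving 10% v 5%: 0.50/0.90 − 0.35/0.95 = 55.6% − 36.8% = 18.7 points before rounding.

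**6. Discontinuation in PP.** It is 0% v 0% whatever the true rates, because the set is defined by not having discontinued.

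**The case against.** The best reply is that the documents leave the safety population unspecified; they do not specify a wrong one. Where they assign populations, they do so for the primary endpoint (SAP 2.1; protocol, Statistical methods) or for choosing covariates for it (SAP 2.4). The protocol's rule on all patients and on deviators' safety data can fill the silence. The SAP's planned attention to safety, loss to follow-up and abandonment makes sense only if those analyses are not confined to mITT or PP.

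Much of this stands. A reader might infer that the SAP directs adverse events and discontinuation onto mITT or PP. It does not. A reader might also infer that mITT deletes everyone who stopped. Discontinuation is not an mITT exclusion, stopping the drug is not the same as leaving the study, and both documents plan imputation of missing data. The explicit between-arm comparison of discontinuation is in the protocol; the SAP calls its analysis descriptive.

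The Kaplan-Meier sentence, taken literally, would treat leavers as censored and leave no events. It is more likely loose English for time-to-event data, since SAP 2.4 goes on to check proportional hazards, which presupposes events.

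The reply does not remove the conflict. The bar in SAP 2.2 is general, the protocol's retention rule has no set in the SAP to carry it out, and the deviations which that rule lists do not name a missing week-12 outcome. The two statements that ITT is used, in SAP 2.1 and the protocol's Statistical methods, concern the primary analysis or endpoint and supply no safety population.

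**Conclusion.** The point holds as a gap joined to a contradiction. No population is named for adverse events, discontinuation or time to abandonment. SAP 2.2 closes off the only defined set with every treated patient, against the protocol's statement that all patients are analysed and deviators' safety data kept.

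The consequence is conditional. If the remaining sets were used, adverse-event rates would be understated. Under the assumed inputs with all stoppers deleted, the hidden difference is 0 points when stopping is equal and 2.4 to 14.5 points across the unequal scenarios. A true 20-point difference would read as about 11 to 19 points if every early leaver were deleted. Discontinuation would be nil in PP and only partly visible in mITT. Partial retention in mITT, as in step 4, gives smaller losses.

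The documents do not support saying that the trial will report a distorted safety profile: that needs both the choice of a depleted set and unequal withdrawal, and they establish neither. This should be fixed. It does not touch the primary efficacy result, and SAP 2.4 treats secondary findings as exploratory.

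**What to change.** - **Safety set (SAP 2.2).** Add all randomised patients who took at least one dose, analysed by treatment received. Make no exclusion for non-compliance, eligibility error or a missing week-12 outcome. Leave out only data for which consent to use was withdrawn. Run all adverse-event tables on this set.
- **Discontinuation.** Run the between-arm comparison and the Kaplan-Meier curve on all randomised patients, with abandonment as the event and completion as censoring. Reword the SAP 2.4 sentence to say so.
- **The bar on ITT.** Limit the SAP 2.2 sentence so that it does not cover safety or discontinuation.
- **Reconcile.** Bring SAP 2.2 into line with SAP 2.1 and with the protocol's Data collection methods and Statistical methods on whether and where the all-randomised population is analysed.

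The cost is SAP wording and one analysis flag. The plan already provides for collecting adverse events and discontinuations, so no new data are needed.

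### The protocol and SAP contradict each other, and themselves, on the primary analysis population and on how non-compliant patients and missing outcomes are counted

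*Combined protocol and SAP*

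**What the plan says.** **Which population**
- SAP 2.1: "The primary analysis will be conducted in the intention-to-treat (ITT), modified intention-to-treat (mITT) and per-protocol populations". None of the three is named as decisive.
- SAP 2.2 defines ITT as all randomised patients, then states: "Because the study is a proof of concept, this population will not be analysed in the IBSET study".
- Protocol, Statistical methods: "Intent-to-treat (ITT), mITT, and per-protocol (PP) analyses were performed for the primary endpoint".
- Protocol, Data collection methods: "All patients will be analysed (intent to treat analysis"). The next sentence says that after a major deviation "only safety data will be evaluated".
- SAP 2.3 specifies the relative risk and the chi-squared or Fisher test but no population. SAP 2.4 mentions mITT for covariate selection only.

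**Non-compliant patients and missing outcomes**
- SAP 2.2 removes from mITT, and again from per-protocol, "Patients with major deviation (primary outcome not available, non-compliance"). The per-protocol list adds only wrong treatment and discontinued treatment to the mITT exclusions.
- Protocol, Statistical methods: "Non-compliant patients were considered non-responders". On missing data: "Missing data (if any) were imputed using Multiple Imputation by Chained Equations (MICE").
- SAP 2.4 leaves the imputation method to be chosen after studying the missing data, lists several candidates, and names no population for it.

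**The concern.** The text does not say which result decides the trial. The same non-compliant patient is a failure in the denominator under the protocol's Statistical methods, is absent under SAP 2.2, and may contribute safety data only under Data collection methods. These choices give different responder rates from the same data.

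If SAP 2.2 is followed, the least restrictive set left is an mITT that conditions on two events occurring after randomisation: non-compliance and an unavailable outcome. Treatment can influence both, so the retained groups need not be comparable. Imputation of the primary outcome would also have nothing to act on, because patients lacking that outcome are outside both remaining sets.

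Proof-of-concept status does not justify this. The trial is sized at 290 patients with 90% power and a two-sided 5% test, and its credibility rests on the randomised comparison.

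**Working it through.** **1. The plan's own figure.** Inputs from the Sample size sections: 35% versus 55%, two-sided 5%, 90% power. The pooled-variance formula gives

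n = [1.960·√(2·0.45·0.55) + 1.282·√(0.35·0.65 + 0.55·0.45)]² / 0.20² = 127.9, so 128 per arm.

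The stated 130 gives 90.5% power, and 130/0.90 = 144.4, so 145 per arm. The plan's figure reproduces.

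**2. Effect of the SAP 2.2 exclusions when there is no true effect.** The documents give no exclusion rate by arm. Assumptions: 145 randomised per arm, 35% true response among all randomised in both arms, 10% excluded on placebo, every excluded patient a non-responder.

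With excluded fraction e, the retained rate is 0.35/(1 − e) and the retained number is 145(1 − e). Rejection probability is 1 − Φ[(1.96·SE₀ − d)/SE₁] + Φ[(−1.96·SE₀ − d)/SE₁], where d is the difference in retained rates (ethosuximide minus placebo), SE₀ is pooled and SE₁ unpooled.

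Worked case, 25% versus 10%:
- ethosuximide 0.35/0.75 = 46.7% of 108.75; placebo 0.35/0.90 = 38.9% of 130.5; d = 0.078
- SE₀ = 0.0642, SE₁ = 0.0641
- (1.96·0.0642 − 0.0778)/0.0641 = 0.75, upper tail 0.227; lower tail 0.001; total 0.228

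| Excluded, ethosuximide / placebo | Retained rates | RR | Two-sided rejection |
|---|---|---|---|
| 10% / 10% | 38.9% / 38.9% | 1.00 | 5% |
| 20% / 10% | 43.8% / 38.9% | 1.12 | 12% |
| 25% / 10% | 46.7% / 38.9% | 1.20 | 23% |
| 30% / 10% | 50.0% / 38.9% | 1.29 | 39% |
| 10% / 30% | 38.9% / 50.0% | 0.78 | 39%, against ethosuximide |

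A simulation of 200,000 trials per scenario agreed for the first four rows (5.1%, 12.1%, 23.0%, 39.6%). Analysing all randomised patients, with excluded patients as non-responders, stayed at 5% in each.

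**3. Relaxing the non-responder assumption.** If excluded patients respond at half the rate of those retained, and the overall rate stays 35%, the retained rate is 0.35/(1 − e/2). At 25% versus 10% this is 0.35/0.875 = 40.0% versus 0.35/0.95 = 36.8%, with rejection about 8%. If excluded and retained patients respond alike, it is 5%.

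**4. Power of an all-randomised analysis.** Suppose 35% and 55% are the rates among evaluable patients and missing outcomes count as non-response, with 145 per arm.
- 10% missing in each arm: 0.35·0.90 = 31.5% versus 0.55·0.90 = 49.5%; power about 88%.
- 25% missing on ethosuximide, 10% on placebo: 31.5% versus 0.55·0.75 = 41.25%; power about 41%.

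**The case against.** Several stronger readings are tempting, and the documents do not support them.

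- **That the plan favours ethosuximide because it is poorly tolerated.** No document gives a tolerability, discontinuation or exclusion rate for either arm. The protocol's Treatment period 1 only foresees stopping or reducing the dose, and for effectiveness as well as intolerance. Equal exclusion leaves the RR unchanged, and greater placebo loss reverses the bias.
- **That the SAP mITT is simply a second per-protocol set.** The two lists are close, but discontinuation excludes from per-protocol, not from mITT. A patient who stops treatment and has a week-12 outcome stays in mITT unless judged non-compliant, and no compliance threshold is given. High discontinuation need not mean high mITT exclusion.
- **That ITT is dropped and the trial also has three chances of success.** These belong to different readings. Under SAP 2.2 two sets remain; under SAP 2.1 there are three and ITT is kept. No passage says success in any one set is enough.
- **That the 35% and 55% planning rates cease to apply.** The plan sizes 130 per arm and then inflates for loss to follow-up, which fits rates among evaluable patients.

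It is also fair to object that 23% comes from assuming both unequal exclusion and no responders among the excluded; step 3 shows how much that second assumption matters. What survives all this is the contradiction itself, and the absence of any all-randomised estimate if SAP 2.2 is followed.

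**Conclusion.** The point holds and must be fixed before analysis. The protocol's Data collection methods and Statistical methods, SAP 2.1 and SAP 2.2 cannot all be followed, and SAP 2.3 does not settle which governs. Under SAP 2.2 the randomised comparison is replaced by one that depends on post-randomisation exclusions.

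The size of the resulting error is conditional. It runs from none (5%) with equal exclusion to 12–39% at 20–30% versus 10%, if all excluded patients are non-responders. At 25% versus 10% it falls to about 8% under the half-rate assumption. These figures illustrate sensitivity to assumed exclusion rates; they do not predict what this trial will show, and the direction is unknown.

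**What to change.** 1. Delete the SAP 2.2 sentence that removes ITT, and the clause in the protocol's Data collection methods that limits major deviators to safety data.
2. Name one primary set in SAP 2.1, 2.2 and 2.3 and in the protocol: all randomised patients, as randomised, except those who withdraw consent to data use.
3. Use observed week-12 NRS and SGA whenever available, and collect them after treatment is stopped.
4. Reconcile the protocol's non-compliance rule with SAP 2.2. Use one wording in both documents, with a stated definition of non-compliance, and keep these patients in the primary denominator. Do not count patients as non-responders only because they discontinued.
5. Pre-specify one primary method for missing week-12 outcomes, for example non-response. Make the protocol's MICE and a missing-not-at-random analysis sensitivity analyses, replacing the open list in SAP 2.4.
6. Keep the non-compliance and unavailable-outcome exclusions in per-protocol only. Label mITT and per-protocol as supportive, and report exclusions by arm and reason.

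The cost is rewording plus week-12 follow-up of patients who stop treatment; no extra patients are needed to make the change. The estimate becomes more conservative. As step 4 of the working shows, the power loss is small with 10% missing in each arm but large if loss is heavy and unequal, so retaining patients for the week-12 assessment matters.

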### *Treatment period 1 - Dose escalation - (D0 to D0+4 weeks)*

Ethosuximide or placebo treatment will be administered daily during dinner, according to a regimen of specific titration for 28 days (maximum dose of 10 ml/day). The patient will assess and record the following daily in the logbook:

- The evening before bed: abdominal pain felt in the last 24 hours with the 11-points NRS,
- The evening before bed: the number, shape and consistency of the stool with the Bristol's scale,
- Side effects or any other particular event should also be carefully noted in the daily logbook,
- Treatment modification.

Every 7 days (at the end of each dose escalation level), patients will be contacted by phone call by investigator in order to collect information on any side effects and inform the patient of the increased dose

in case of inefficiency and good tolerance. Stopping or decrease dosage will be used in cases of intolerance or effectiveness of the treatment.

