#### *Phone call follow-up to D0+15 weeks ( $\pm 1$ week)*

This phone call aims to recover daily scores of abdominal pain during the last 7 days. This phone call closes the patient's study participation.

- All patients followed the same procedures (assessment of pain, filling questionnaires and taking treatment in the indicated dosage level).
- No deviation to the protocol will be allowed during the entire study.
- To verify patient compliance, accounting treatment units will be made at each planned visits.
- No change of treatment will be allowed during the test.

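### The protocol scores non-compliant patients as non-responders; SAP 2.2 removes them from both the mITT and per-protocol sets, drops ITT, and leaves non-compliance undefined

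*Combined protocol and SAP*

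**What the plan says.** Protocol, Statistical methods: "Intent-to-treat (ITT), mITT, and per-protocol (PP) analyses were performed for the primary endpoint". The next sentence but for the effect measure reads "Non-compliant patients were considered non-responders", and it is not tied to any one of the three sets.

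SAP 2.1: "The primary analysis will be conducted in the intention-to-treat (ITT), modified intention-to-treat (mITT) and per-protocol populations".

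SAP 2.2 defines ITT as everyone randomised, then adds: "Because the study is a proof of concept, this population will not be analysed in the IBSET study". Its exclusion lists for mITT and for per-protocol both end with "Patients with major deviation (primary outcome not available, non-compliance". Discontinuing study treatment is a separate exclusion and appears only in the per-protocol list.

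SAP 2.3 (primary analysis) gives no rule for scoring non-compliant patients.

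On how compliance is judged, the protocol (under the week-15 phone call) says only: "To verify patient compliance, accounting treatment units will be made at each planned visits". No threshold, reference dose or time window follows. Under Treatment period 1 the protocol also provides: "Stopping or decrease dosage will be used in cases of intolerance or effectiveness of the treatment".

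**The concern.** The two documents give different instructions for the same patients in the primary analysis. One keeps them in the denominator as failures; the other takes them out. Non-compliance is known only after randomisation, so removing these patients gives up the protection of randomisation for that part of each arm. Excluding them is ordinary in a per-protocol analysis. Here it also applies to mITT, the only other set that SAP 2.2 leaves.

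The missing definition makes this worse. Dosing is titrated patient by patient and can be reduced or stopped on instruction, so patients who did as they were told will return different numbers of units. Without a stated reference dose, a unit count does not separate them from patients who did not take what was prescribed.

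At stake is whether the primary relative risk and its p-value depend on a choice between two written rules that is still open when the data are seen.

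**Working it through.** **1. The texts side by side.** If ITT is analysed, the protocol's scoring rule could apply there and removal could apply in mITT and per-protocol. SAP 2.2 closes that route by cancelling ITT. SAP 2.1 reopens it, but the SAP then has no rule for scoring non-compliant patients in ITT. Under SAP 2.2 as written, no non-compliant patient reaches the primary comparison.

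**2. The plan's own sample size.** Inputs (Sample size section): 35% against 55%, two-sided 5%, 90% power, 130 per group, 145 after a 10% allowance.

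Pooled-variance formula: n = [1.96·√(2·0.45·0.55) + 1.2816·√(0.35·0.65 + 0.55·0.45)]² / 0.20² = 127.9, so 128 per group. At 130 per group power is 90.5%. 130/0.90 = 144.4, so 145. The stated figures reproduce.

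**3. Effect of the rule on the relative risk.** In an arm with responder rate r among compliant patients and non-compliant share c, removal estimates r and scoring estimates r(1−c). Hence

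RR(scored) = RR(removed) × (1−c1)/(1−c0),

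with c1 for ethosuximide and c0 for placebo. This holds whatever pain or SGA scores the non-compliant patients report at week 12.

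**4. Size.** Assumptions: 55% and 35% among compliant patients, 130 per group, and illustrative shares of 5% to 20%, because the documents give none. Removal uses 130(1−c) per arm and always shows 20 points and RR 0.55/0.35 = 1.57. Scoring uses 130 per arm with rates 0.55(1−c1) and 0.35(1−c0).

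| c1 / c0 | Power, removed | Scored rates | Difference | RR, scored | Power, scored |
|---|---|---|---|---|---|
| 10% / 10% | 87% | 49.5% v 31.5% | 18.0 | 1.57 | 84% |
| 10% / 5% | 88% | 49.5% v 33.25% | 16.25 | 1.49 | 76% |
| 20% / 10% | 85% | 44.0% v 31.5% | 12.5 | 1.40 | 55% |
| 5% / 10% | 88% | 52.25% v 31.5% | 20.75 | 1.66 | 93% |

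With all 145 per group, power (removed, then scored) is 91% and 88% at 10%/10%, and 89% and 59% at 20%/10%. The pattern does not depend on which n is used.

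**5. Error rates under no effect depend on what no effect means.** Take 20%/10% and 130 per group.
- Suppose 35% of all randomised patients respond in each arm, with non-compliant patients counted as failures. Removal then shows 0.35/0.80 = 43.8% against 0.35/0.90 = 38.9%, and the chance of a significant result favouring ethosuximide is 11% instead of 2.5%.
- Suppose instead that 35% of compliant patients respond in each arm. Scoring then shows 0.35·0.80 = 28.0% against 0.35·0.90 = 31.5%, and the chance of a significant result favouring placebo is about 9%.

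The documents do not say which of these is the null of interest.

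**The case against.** The strongest reply has four parts.

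*ITT may still be analysed.* SAP 2.1 and the protocol both list it, and scoring in ITT with exclusion in per-protocol is a normal pairing. That is fair, but SAP 2.2 says the opposite, and SAP 2.1 supplies no scoring rule. The disagreement over ITT is itself part of the defect.

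*The SAP exclusion may have a source in the protocol.* Data collection methods says that "if a major deviation from the protocol (non-respect of co-occurring treatment, inclusion / exclusion criteria and the study design) only safety data will be evaluated", and SAP 2.2 files non-compliance under major deviation. This stands in part. The protocol's list does not name study-drug non-compliance, which Statistical methods handles separately by scoring, but a deviation from the study design could be read to cover it. The text should settle this.

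*Intolerance need not produce an imbalance.* A reader might infer that ethosuximide's side effects will make many more patients non-compliant on active drug, so that the SAP will inflate the result. The documents do not support that. SAP 2.2 separates discontinuation from non-compliance and excludes for discontinuation only in per-protocol. On that reading, a patient who stops for intolerance but has a week-12 outcome stays in mITT. A stop or decrease directed under Treatment period 1 is also following the protocol. With no definition the risk remains open, but it is not demonstrated.

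*The large figures rest on assumed shares.* This stands. With equal shares the relative risk does not move, the reverse imbalance moves it the other way, and the 11% false-positive figure presupposes that the protocol's scoring rule defines the truth.

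**Conclusion.** The conflict holds on the text alone: the protocol scores these patients, SAP 2.2 removes them from every set it will analyse, and neither document says who they are. The change in relative risk by (1−c1)/(1−c0) is exact. Its size in this trial is unknown, because no non-compliant share is given. Under equal shares the consequence is small: the same relative risk, and about 3 points of power at 10%. Under unequal shares it can be material. A 10%/5% split moves the relative risk from 1.57 to 1.49, and a 20%/10% split moves it to 1.40, given 55% and 35% among compliant patients. These are illustrations, not forecasts, and neither the direction nor a large imbalance is established. The point should be settled before unblinding, because the remedy is cheap and the protocol already contains a rule that avoids this exclusion.

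**What to change.** In SAP 2.2:
- Delete non-compliance from the mITT exclusions and keep it for per-protocol.
- Score non-compliant patients as non-responders in mITT, as the protocol does, and state that this overrides the exclusion for an unavailable primary outcome. That exclusion sits in the same bullet, so without the override non-compliant patients lacking week-12 data would still drop out.
- Define non-compliance before unblinding as taking less than a stated percentage of the units directed for that patient. A decrease or stop directed under Treatment period 1 is then not non-compliance.
- Add a sensitivity analysis that classifies these patients on their observed week-12 NRS and SGA.

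Make SAP 2.1 and 2.2 agree on whether ITT is analysed; if it is, apply the same scoring rule there. In the protocol's Data collection methods, state that study-drug non-compliance is not a deviation that limits a patient to safety data. The dosing rule in Treatment period 1 needs no change.

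Cost: SAP and protocol wording, with the protocol sentence handled through the usual amendment route. Unit counts are already collected, and no patients or visits are added. Scoring shrinks the absolute difference (20 to 18 points at 10%/10%) and lowers power somewhat (87% to 84% there, with 130 per group).
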